### Sample size

To find a difference between groups of medium effect size with a power of 0.8 at an alpha of 0.05, both the treatment and the control arm need to include 64 patients, as calculated with.

G*power 3.1.5. Dropout rates in regular addiction treatment are known to be approximately 20%. Given the 6 and 12 months follow-up measurements a dropout rate of 40% was calculated. Therefore, a total amount of 213 patients will be recruited.

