### Randomization

Participants who meet the inclusion criteria will be automatically assigned to one of the three conditions with the following likelihood (1) 50% TAU + iABM, (2) 25% TAU + placebo condition and (3) 25% TAU-only. Furthermore, the registration and monitoring system stratifies for gender, age group (18–30, 30–50, 50+), type of addiction, and institution. Therefore, participants are assigned to one of the three conditions to which the fewest participants of their gender, age group, and type of addiction are assigned accounting for the institution of the participants. When proven effective, participants in the control conditions (TAU + placebo condition and TAU-only) will be offered the iABM intervention after the end of the study (approx. End 2018).

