### Data analyses

#### Clinical analysis

First, changes in attentional bias, as measured with the *odd one out task*, will be examined by using a 4 (within subjects: pre, post, FU1, FU2) × 2 (between subjects: TAU + iABM versus control conditions) repeated measure ANOVA, with attentional bias as dependent variable. To assess the validity of the main hypothesis, a 4 (within subjects: pre, post, FU1, FU2) × 2 (between subjects: TAU + iABM versus control conditions) repeated measure ANOVA will be conducted to examine the effects of the iABM intervention on substance use and craving, as measured with the MATE. In order to evaluate the effects of iABM intervention on rates of relapse, a Cox regression analysis will be conducted to model the time until relapse occur.

Further, changes in secondary physical and psychological complaints (depression, anxiety and stress) will be tested by a 4 (within subjects: pre, post, FU1, FU2) × 2 (between subjects: TAU + iABM versus control conditions) repeated measure ANOVA, based on the MATE. Missing data will be handled with multiple imputation.

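### The ANOVAs omit the four factors used to balance allocation; if those factors predict outcome, the between-group comparison of levels is conservative and less efficient than an adjusted one

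*Protocol article*

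**What the plan says.** **Allocation** (Protocol article, Randomization). The section states that "the registration and monitoring system stratifies for gender, age group (18–30, 30–50, 50+), type of addiction, and institution". It describes a minimisation-type rule: "participants are assigned to one of the three conditions to which the fewest participants of their gender, age group, and type of addiction are assigned", with institution also taken into account. Half of the patients go to iABM and a quarter to each control condition, so iABM against the pooled controls is 1:1.

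**Analysis of continuous outcomes** (Clinical analysis). For substance use and craving, a 4 × 2 "repeated measure ANOVA will be conducted to examine the effects of the iABM intervention on substance use and craving, as measured with the MATE". The four levels are the visits; the two are iABM and the combined control conditions. The same 4 × 2 form is given for attentional bias and for depression, anxiety and stress. No allocation factor appears in any of them. Missing data are to be multiply imputed.

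**Analysis of relapse** (Clinical analysis). "a Cox regression analysis will be conducted to model the time until relapse occur". Covariates and strata are neither listed nor excluded.

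**Sample size.** A plain two-group calculation: "medium effect size with a power of 0.8 at an alpha of 0.05, both the treatment and the control arm need to include 64 patients", raised to 213 recruited for 40% dropout.

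**The concern.** Balancing on prognostic factors removes their contribution from the difference between arms. A model without those factors still counts that contribution as residual variation. Its standard error is then larger than the true sampling variation of the arm difference, so the test rejects less often than its nominal level and gives up precision that the allocation scheme has already secured.

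The 4 × 2 notation names every factor in the ANOVA design, so the omission belongs to the stated model and is not a covariate list left for another document. The comparison of levels matters here because the section on trial objective and hypothesis predicts less use and less craving at post-measurement and at 6 and 12 months, which is a statement about levels. What is at stake is efficiency and the accuracy of the error rate. The error is in the conservative direction, so false positives are not the worry.

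**Working it through.** **Inputs from the protocol article.** Power 0.8, alpha 0.05, 64 per arm, 40% dropout, 213 recruited (Sample size); four allocation factors, with iABM to pooled control 1:1 (Randomization); four centres (Trial design).

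**Assumptions, because the article gives no figure.** Medium effect is d = 0.5 and alpha is two-sided. R² is the share of outcome variance that the four factors explain together; it is varied from 0 to 0.30 and split equally among them. The simulation also assumes factor frequencies of 70/30 (gender), 30/45/25 (age group), 70/30 (addiction type) and equal quarters (institution), a probability of 0.8 of taking the best-balancing arm, and a within-person correlation of 0.5.

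**Step 1: the plan's own figure.** A two-sided two-sample t test with d = 0.5 and 80% power needs 63.8 per arm, so 64 (power 0.801). Then 128 / (1 − 0.40) = 213.3. The stated 64 and 213 reproduce.

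**Step 2: closed form under perfect balance.** The noncentrality is 0.5 × √(64/2) = 2.828. The unadjusted test divides by a standard error that still contains the factor variance, so its statistic has standard deviation √(1 − R²) instead of 1:

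- unadjusted type I error = 2[1 − Φ(1.96/√(1 − R²))]
- unadjusted power = Φ((2.828 − 1.96)/√(1 − R²))
- adjusted power = Φ(2.828/√(1 − R²) − 1.96)

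| R² | Type I error, unadjusted | Power, unadjusted | Power, adjusted |
|---|---|---|---|
| 0 | 5.0% | 80.7% | 80.7% |
| 0.05 | 4.4% | 81.4% | 82.7% |
| 0.10 | 3.9% | 82.0% | 84.6% |
| 0.20 | 2.8% | 83.4% | 88.5% |
| 0.30 | 1.9% | 85.0% | 92.2% |

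**Step 3: simulation of the allocation scheme.** 2:1:1 minimisation on the four factors, 213 recruited, 40% lost, 3000 runs per row, comparing levels between iABM and pooled controls.

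| R² | Type I error, unadjusted / adjusted | Power, unadjusted / adjusted |
|---|---|---|
| 0 | 4.6% / 4.8% | 79.3% / 79.1% |
| 0.05 | 5.3% / 5.7% | 79.5% / 80.3% |
| 0.10 | 3.8% / 4.5% | 79.4% / 81.8% |
| 0.20 | 3.2% / 5.1% | 81.0% / 86.8% |
| 0.30 | 2.7% / 4.7% | 81.1% / 91.0% |

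Simulation error is √(0.05 × 0.95/3000) = 0.4 points on a 5% rate and √(0.8 × 0.2/3000) = 0.7 points on 80% power, so the rows at 0 and 0.05 show no material effect. With the best-balancing arm always taken, power is 80.4% / 83.2% at R² = 0.10 and 80.7% / 87.0% at 0.20, and unadjusted type I error is 4.3% and 3.4%. The closed form and both simulations thus put the power gap at about 2.3 to 2.8 points at R² = 0.10 and 5.1 to 6.4 points at 0.20.

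**Step 4: the time × group interaction.** If a factor shifts a patient's level equally at every visit, it cancels from the change score. In the same simulation of pre-post change, with R² from 0 to 0.30, unadjusted type I error is 5.0–5.6% and power 79–81%; adjusted power is 78–79%. Adjustment gains nothing there. If factor effects emerge only after baseline, they enter the change score and the Step 2 formulas apply with R² read as the share of change-score variance. At R² = 0.15, for example, √0.85 = 0.922, which gives type I error of 3.4% and power Φ(0.868/0.922) = 83% unadjusted against Φ(2.828/0.922 − 1.96) = 87% adjusted.

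**The case against.** **The efficacy test may be the interaction.** The section on primary and secondary outcome measures speaks of changes, and baseline is one of the four visits in the ANOVA, so the natural treatment test is time × group. The between-group main effect averages in the pre-treatment visit. With stable factor effects the interaction is untouched, and this largely stands. It does not dispose of the point: the stated hypothesis is about levels after treatment, and stability is doubtful for institution. TAU varies from 350 to 750 minutes with optional extra components, and therapists counsel on adherence, so centre differences could arise after baseline.

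**There is no shortfall against the plan.** This stands. A reader might infer that the trial falls below its planned power, or that every between-arm test runs under 5%. The documents do not support either: unadjusted power for the comparison of levels stays at about 79–81% in the simulation, and the interaction keeps its nominal level under stable factor effects.

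**The size is assumed.** This stands too. The article gives no variance share for any factor, and near R² = 0 nothing is lost.

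**The Cox regression.** A reader might infer that the relapse model is unadjusted, loses power and gives a hazard ratio pulled towards 1. An unadjusted model could behave in that way: with an assumed hazard ratio of 0.55, baseline hazard of 0.6 per year and a factor standard deviation of 0.5 on the log-hazard scale, power was 62% against 67% adjusted. But the article does not say that the model is unadjusted, and an article may leave a covariate list to the full protocol or analysis plan. An unadjusted and an adjusted hazard ratio are also different quantities, so bias would be a loose word for the gap. This is no error in the plan.

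**Conclusion.** The point holds in a limited form. The ANOVAs are fixed without the four factors that allocation is balanced on. Provided those factors predict outcome, the between-group comparison of levels is conservative and less efficient than it need be: at an assumed joint R² of 0.10–0.20, type I error is about 3–4% and power about 3–6 points below an adjusted analysis. The result rests on d = 0.5, a two-sided 5% test, about 128 completers and the assumed R². The interaction is affected only if factor effects change over time. This is a nearly free improvement and does not threaten the trial's validity.

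**What to change.** In Clinical analysis, state that the models for attentional bias, substance use, craving, and depression, anxiety and stress include gender, age group, type of addiction and institution, coded as in the allocation system, as **main-effect covariates**.

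- Include all four factors; leaving out type of addiction would still ignore part of the allocation.
- Say explicitly that no interactions among the factors are fitted. A full factorial would have 2 × 3 × 2 × 4 = 48 cells for 128 completers.
- Add factor-by-time terms if the effects may change over time. In a repeated-measures ANOVA, main-effect terms alone alter only the between-subject error and leave the time × group test as it was.
- Put the same four variables in the multiple-imputation model.
- For the Cox regression, state that the same factors enter as covariates or strata, for consistency with the other models.

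**Cost.** A few sentences and 1 + 2 + 1 + 3 = 7 between-subject degrees of freedom out of 128 − 2 = 126. Factor-by-time terms, if used, take 7 × 3 = 21 of the 126 × 3 = 378 within-subject degrees of freedom. The allocation system already holds the data, and no extra patients are needed. The wording should be fixed before any unblinded analysis, so that the covariates are not chosen after the results are seen.

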#### Economic evaluation

If the iABM intervention was shown to be effective, the economic evaluation will be performed from a societal perspective, which means that all relevant costs will be taken into account, regardless of who pays for them. Health-care costs, such as contacts with health care professionals, and costs of lost productivity will be calculated by multiplying the volumes of health-care with standard unit prices derived from the Dutch Manual for cost research [52].

The time horizon of the economic evaluation will be 12 months and will compare the iABM intervention to TAU-only. Cost-effectiveness and cost utility will be assessed by relating the incremental costs of the two treatments to the incremental outcomes. The primary outcome measure in the cost effectiveness analysis will be substance use and relapse rates, as measured with the MATE and additional questions regarding relapse. In addition, a cost utility analysis will be performed with quality-adjusted life years (QALYs) as primary outcome, based on the EQ-5D-3 L defined utilities. No discounting of costs and effects will be conducted, since the time horizon does not exceed 1 year.

Uncertainty surrounding the cost-effectiveness and cost utility ratios will be assessed using bootstrap analysis. In addition, cost-effectiveness acceptability curves will be used to inform decision-makers on the probability that iABM intervention is cost effective.

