## Methods and design

### Trial design

The present study is a multicentre randomized controlled two-armed, parallel-designed trial with one treatment arm (iABM intervention) and a control arm, which will be divided into a placebo condition and a TAU-only condition (see Fig. 1). The inclusion of these two control conditions enables (1) the investigation of the effect of TAU + iABM intervention, related to TAU-only, and (2) the control for a possible placebo effect, by comparing the iABM condition with the placebo condition. The design of the study enables that iABM intervention, as well as the placebo condition, can be provided parallel to treatment as usual (TAU). Recruitment will take place in four addiction care centres in the Netherlands (*Iriszorg*, *Novadic-Kentron, Tactus Verslavingszorg and Verslavingszorg Noord Nederland*). There are two treatment intensities in the Dutch mental health care system. All participants who will be included in this study will receive the lower dose treatment, in which TAU consists of 350 to 750 min of protocolled CBT-based intervention in a specialized addiction care institution, including a 30% range of possible additional interventions, such as medication. Whether therapists make use of such additional intervention components depends on the severity of addiction and possible related problems of the patients. Patients who are ascribed to this intensity of treatment are expected to live relatively independent and to report less comorbidity. The additional effects of the iABM intervention will be tested directly after the end of TAU, which is also the end of the training, and 6 and 12 months later. For an overview of the planned timeline of the study, see Fig. 2.

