After assignment to the system, all participants will be invited by e-mail to complete the baseline assessment. Participants who are assigned to the TAU-only condition will thereafter receive TAU. Participants who are assigned to one of the trainings (active or placebo) will thereafter read the training instructions. Furthermore, they can watch an animated video in which the training is explained. Hereafter a short 5-min practice session of the training follows. One day after completing the baseline assessment and the practice session of the training, participants in one of the training conditions will receive an invitation for the first training session by e-mail. The following three weeks, participants will be asked to train on a daily basis. Thereafter, the number of training sessions per week will decline. Participants will train three times a week for another three weeks and finally once a week until the end of TAU. Thus, the actual number of training sessions is dependent on the duration of TAU. The lower doses treatment in the Dutch addiction care usually takes 3 to 6 months, depending on the severity and the progress of the patient. During the whole training period a researcher will monitor the process of the patients and whether they train regularly. After three training sessions are missed, patients will receive an automatic reminder by e-mail. If this does not result in the continuation of the training the researcher will contact the patient via the preferred way (phone, e-mail, text message or app) in order to ask whether there are any problems or doubts about the participation in the study.

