An important part of the study is the involvement of the therapists. In order to improve adherence, the researchers will train the therapists before the inclusion of participants starts. The training will consist of the following parts (1) general background knowledge about attentional bias and ABM, (2) design and important parts of the study, and (3) the role of the therapists. During the training all therapists will receive a protocol in which all important aspects are described. In the first session of TAU after patients are assigned to the study, therapists will identify the time of the day patients’ craving is strongest and will instruct the patient to complete the ABM task at this particular time of the day. Furthermore, during each following treatment session of TAU, the therapist will ask the participant whether he/she trains on a regular basis, and will engage in motivational counselling if this is not the case.

During the last week of TAU in addiction care, participants in the training conditions will receive the last training invitation by e-mail. After completion, they will be invited for the post-assessment. Participants in the TAU-only condition will also receive the invitation for the post-assessment in their last week of TAU. Finally, 6 and 12 months after the end of TAU, all participants will receive an invitation for the follow-up measurements by e-mail. In case a participant does not respond to these invitations, the researcher will remind the patient via the preferred way (phone, e-mail, text message or app). Throughout the length of the whole project, a sounding board group will meet four times to monitor the process of the study. The group will include a researcher, a therapist, and a member of the client council of each addiction care centre, and an implementation professional.

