#### Other measurements

During the baseline assessment, sociodemographic information will be collected, such as gender, relationship, level of education, and work. Furthermore, details of the patients’ own clinical history of addiction as well as of their family will be asked. Next, participants who are assigned to one of the training conditions will be asked about their expectations of the intervention. Before and after each training session, participants will rate their intensity of craving on a visual analogue scale (VAS), varying from 0 (no craving at all) to 100 (extreme craving). With this, possible direct effects of the intervention on subjective craving can be examined. Furthermore, at the end of the baseline assessment, all participants are asked to fill in a short questionnaire about their computer/laptop use in their private life. This information might be helpful when investigating for whom this iABM intervention was effective. Last, after the first week of training and during the post-assessment, participants, who are assigned to one of the training conditions, will be asked to fill in an evaluation questionnaire, in which they can give their opinion about the intervention and are asked to indicate whether the intervention helped them. Information derived from these questionnaires can be used as indications for possible next steps towards implementation. For an overview of all questionnaires and tasks per time point, see Table 2.

**Table 2 Tab2:** Overview of measurement instruments per time point

Purpose	Measures	Baseline	Post-assessment	Follow-up
Attentional bias assessment	Odd one out task	X	X	X
Baseline measures	Demographics	X		
	History of addiction	X		
	Family history of addiction	X		
Primary outcome measures - clinical	MATE (substance use, craving)	X	X	X
	Clinical state (relapse)			X
Primary outcome measures - Societal/economical	TiC-P	X	X	X
	EQ-5D	X	X	X
Secondary outcome measures	MATE (depression, anxiety and stress)	X	X	X
	Computer use	X		
Others	Expectation-questionnaire	X^a^		
	Training evaluation		X^a^	

^a^only to be filled in by participants in one of the training conditions

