### Primary and secondary outcome measures

The effectiveness of the iABM intervention will be examined by changes in substance use (i.e. quantity of use in the past 30 days), craving, and relapse rates. Measurements of attentional bias will serve as a manipulation check for the effects of iABM intervention.^1^ Secondary outcome measures are cost-effectiveness,^2^ and secondary physical and psychological complaints (depression, anxiety, and stress). The evaluation forms of the patients and therapists will be assessed as well.

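### The 12-month economic horizon has no stated start and cannot span the 15 to 18 months from baseline to last follow-up, and the evaluation is run only if iABM proves effective

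*Protocol article*

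**What the plan says.** All references are to the protocol article.

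- **Horizon and comparator** (Economic evaluation): "The time horizon of the economic evaluation will be 12 months and will compare the iABM intervention to TAU-only". No start point is given. The same section promises a societal perspective covering all relevant costs, and omits discounting on the ground that the horizon is no longer than a year.
- **Length of treatment** (Participants and procedure): "The lower doses treatment in the Dutch addiction care usually takes 3 to 6 months". Training fills the same period: "Participants will train three times a week for another three weeks and finally once a week until the end of TAU".
- **Follow-up** (Participants and procedure): "6 and 12 months after the end of TAU, all participants will receive an invitation for the follow-up measurements". Trial design uses the same anchor, with effects tested "directly after the end of TAU, which is also the end of the training, and 6 and 12 months later".
- **Condition** (Economic evaluation): "If the iABM intervention was shown to be effective, the economic evaluation will be performed from a societal perspective".
- **Aim** (Trial objective and hypothesis): the authors predict that the fall in societal costs will exceed what iABM adds.
- **Status of the outcome**: Table 2 places the TiC-P and EQ-5D under "Primary outcome measures - Societal/economical", while the outcomes section says "Secondary outcome measures are cost-effectiveness".

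**The concern.** The horizon is shorter than the trial's own observation period, and the text does not say which part is given up. The two possible starts answer different questions. One loses the longest follow-up, which the Discussion presents as a strength of the study. The other loses the period in which the added treatment is delivered and paid for. Two analysts could follow the same sentence and report different incremental costs and QALYs.

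The condition is a separate problem. Cost-effectiveness is a stated objective and a prespecified outcome, and a non-significant clinical result does not settle it. The bootstrap and acceptability curves already planned express uncertainty without needing a significant effect. If the evaluation runs only after a favourable clinical result, the objective is either left unanswered or reported from a selected result. The condition names no endpoint or time point, although there are three clinical primary outcomes. The planned ANOVAs compare iABM with the two control conditions pooled, whereas the economic comparison is with TAU-only.

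**Working it through.** **1. The plan's own sample size.** A two-sided two-sample t-test with d = 0.5 (taken as the medium effect), alpha 0.05 and power 0.80 needs 63.8, so 64 per arm. Then 2 × 64 = 128, and 128 / (1 − 0.40) = 213.3, which agrees with the stated 213. This matters here only because step 4 uses 64 per arm.

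**2. Timeline.** Let T be the duration of TAU in months, usually 3 to 6. Assessments fall at 0, T, T + 6 and T + 12.

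| T | Post | First follow-up | Last follow-up | Share of window in 12 months | Months outside |
|---|---|---|---|---|---|
| 3 | 3 | 9 | 15 | 12/15 = 80% | 3 |
| 6 | 6 | 12 | 18 | 12/18 = 67% | 6 |

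Baseline may follow the first TAU sessions, because consent is accepted up to the third, so the true interval can be slightly shorter. The conflict does not depend on the exact range: any T above zero puts the last follow-up beyond month 12.

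**3. The two possible starts.**
- *From baseline:* the treatment period is covered, but the horizon ends 3 to 6 months before the last follow-up. The last assessment inside it is the 6-month follow-up, at month 9 to 12. When T is 3, no scheduled assessment falls at month 12.
- *From the end of TAU:* the last follow-up is reached, but the treatment period is outside. That is 3/15 = 20% to 6/18 = 33% of observed time.

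A horizon from baseline to last follow-up would be 15 to 18 months, so the one-year reason for not discounting would no longer apply.

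**4. Illustration of the condition.** Assume that being shown effective means significance on one two-sided t-test at 0.05 with 64 per group. The noncentrality is d × √(64/2) and the critical value is 1.98 on 126 degrees of freedom. The mean effect given significance comes from simulation, in SD units.

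| Assumed true d | Noncentrality | Power | Evaluation skipped | Mean effect given significance |
|---|---|---|---|---|
| 0.3 | 1.70 | 0.39 | 61% | 0.47 |
| 0.4 | 2.26 | 0.61 | 39% | 0.51 |
| 0.5 | 2.83 | 0.80 | 20% | 0.56 |

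The last row is the design effect. Even there the evaluation would be skipped about one time in five.

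**5. Size of the discounting question.** Assume costs are spread evenly and months 13 onward are discounted by one full year, at assumed rates of 1.5% to 4%. The change in total cost runs from (3/15) × (1 − 1/1.015) = 0.3% to (6/18) × (1 − 1/1.04) = 1.3%.

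**The case against.** The best defence is that a horizon need not equal total follow-up. Twelve months from baseline would contain the usual TAU and training period with its costs, so it is shorter but not invalid, and the no-discounting sentence is consistent with the horizon as stated. The start point could also be given in a fuller protocol or economic plan that is not at hand. The timeline figure and the footnote attached to cost-effectiveness in the outcomes section could not be consulted either. This stands against calling the horizon an error. It does not resolve the conflict, because the article fixes the horizon, the visit schedule and the discounting reason itself, and no 12-month window covers both treatment and the last visit.

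A reader might infer that an end-of-TAU start drops the whole cost of iABM. The documents do not support that: the section promises all relevant costs, the hypothesis names the cost of iABM, the TiC-P is collected at baseline and post-assessment, and iABM cost could be added separately. What is missing is a statement of how it enters.

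A reader might also take the table in step 4 as a forecast, or carry the inflated effect straight into the cost-effectiveness ratio. Neither is justified. The plan uses 4 × 2 repeated-measures ANOVAs and a Cox model, and if any one of several outcomes could satisfy the condition, the evaluation would run more often than shown. The inflation applies to a pooled-control difference. The economic contrast is with TAU-only, which receives 25% of participants against 50% for the two control conditions together, and it also uses QALYs. The selection carries over only in part.

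Finally, comparing iABM with TAU-only is not an error in itself, since Trial design lists that comparison as a purpose of the study. The condition is openly stated and leaves the primary clinical analysis untouched.

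**Conclusion.** The point holds in this form: the 12-month horizon has no stated start and, on either reading, leaves 3 to 6 months of a 15 to 18 month window outside. These are either the final months, including the 12-month follow-up, or the treatment period (20 to 33% of observed time). Which part is lost cannot be determined from the text. This rests only on the stated TAU duration and follow-up anchor.

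The condition on effectiveness is confirmed. It puts a stated objective at risk of being unanswered or selectively reported. The skip rates of 61%, 39% and 20% depend on the assumed d and a single t-test, and show direction and order only.

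It would go too far to call the 12-month figure invalid, to say that iABM costs are excluded, or to put a percentage on the bias in the cost-effectiveness ratio. The discounting effect is small, and the Table 2 label is an editorial mismatch. The matter concerns the economic objective, not the clinical conclusions, and should be corrected because the correction is cheap.

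**What to change.** - Define the horizon as baseline (or randomisation) to the 12-month follow-up, and state that iABM costs and TAU-period costs are included.
- Replace the one-year reason for not discounting: either discount costs and effects after month 12, or show results both ways.
- Delete the condition on effectiveness. Run the evaluation against TAU-only, with the planned bootstrap and acceptability curves, whatever the clinical result.
- Editorially, give cost-effectiveness the same status in Table 2 and in the outcomes section.

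The cost is protocol wording and modest extra analysis. The TiC-P and EQ-5D are already scheduled at baseline, post-assessment and follow-up, so no new data collection is implied. The article does not give the TiC-P recall period, so the authors should check that it covers the gaps between assessments.
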